### Interventions

#### Usual care control group

The usual care control group (no formal exercise training) receive routine care throughout their cancer pathway from diagnosis to surgical resection. No specific advice about exercise training is offered.

#### Exercise intervention group

The exercise training programme was designed to improve physical fitness in the time interval between end of neoadjuvant CRT and surgery. Exercise training begins on the first week following completion of neoadjuvant CRT, and the patients exercise in pairs for camaraderie. The exercise training programme is described below.

#### Exercise training protocol

The delivery of the exercise training programme is described using the FITT principle (frequency, intensity, time and type of exercise training (American College of Sports Science, 2009)) detailed below.

#### Exercise training frequency

Patients are requested to attend three in-hospital exercise training sessions per week for 6 to 9 weeks (dependent on the time interval between neoadjuvant CRT and surgery at each hospital).

#### Exercise training intensity

The exercise training is an aerobic interval exercise training programme incorporating moderate and severe intensities. Exercise training intensities are derived from each individual CPET derived at Week 0 (immediately post-CRT). Moderate-intensity exercise is at a power output equivalent to 80 % of the oxygen uptake at lactate threshold ($$ \overset{\cdotp }{\mathrm{V}}{\mathrm{o}}_2 $$ at $$ {\widehat{\uptheta}}_{\mathrm{L}} $$). Severe-intensity exercise is at a power output half-way between $$ \overset{\cdotp }{\mathrm{V}}{\mathrm{o}}_2 $$ at $$ {\widehat{\uptheta}}_{\mathrm{L}} $$ and $$ \overset{\cdotp }{\mathrm{V}}{\mathrm{o}}_2 $$ at peak (termed 50%Δ). Algebraically, this is calculated as follows:

Moderate-intensity exercise: (Work load at $$ \overset{\cdotp }{\mathrm{V}}{\mathrm{o}}_2 $$ at $$ {\widehat{\uptheta}}_{\mathrm{L}} $$ −$$ \raisebox{1ex}{$2$}\!\left/ \!\raisebox{-1ex}{$3$}\right. $$ of work ramp) × 80 %

Severe-intensity exercise: ((Work load at $$ \overset{\cdotp }{\mathrm{V}}{\mathrm{o}}_2 $$ at Peak-Work load at $$ \overset{\cdotp }{\mathrm{V}}{\mathrm{o}}_2 $$ at $$ {\widehat{\uptheta}}_{\mathrm{L}} $$ −$$ \raisebox{1ex}{$2$}\!\left/ \!\raisebox{-1ex}{$3$}\right. $$ of work ramp) × 50 %) + Work load at $$ \overset{\cdotp }{\mathrm{V}}{\mathrm{o}}_2 $$ at $$ {\widehat{\uptheta}}_{\mathrm{L}} $$.

Each exercise session included a 5-minute warm-up and cool-down using unloaded pedalling. Exercise training intensities are responsive to each CPET (informed by measured work rates at $$ \overset{\cdotp }{\mathrm{V}}{\mathrm{o}}_2 $$ at $$ {\widehat{\uptheta}}_{\mathrm{L}} $$ and $$ \overset{\cdotp }{\mathrm{V}}{\mathrm{o}}_2 $$ Peak at Weeks 3 and 6) during the exercise programme and are derived and reported by two assessors. The absolute power output for subsequent training sessions are adjusted according to the outcome of the CPET.

#### Exercise training time

The first two training sessions involve 30 minutes of exercise which increases to 40 minutes per session thereafter. In the first week of training, patients perform the interval exercise training protocol for 20 minutes with a 5-minute warm-up and cool down. The interval exercise training phase includes four repeated bouts of moderate to severe intensity. Following week 1, the time of each exercise training session increases to 30 minutes with a 5-minute warm-up and cool down. The interval exercise training phase includes six repeated bouts of moderate- to severe-intensity intervals.

#### Exercise training type

The exercise training programme is conducted on a computer-controlled, electromagnetically braked, cycle ergometer (Optibike Ergoselect 200; Ergoline, GmbH, Bitz, Germany) (see Fig. 2). Heart rate is continuously recorded from the R-R interval (Polar FT7, Warwick, UK). The training programme is preloaded on to a chip-and-pin card that executes the interval intensities automatically onto the screen displayed on the cycle ergometer (see Fig. 3).

**Fig. 2 Fig2:**
[figure not shown]
Exercise training cycle ergometers (Optibike Ergoselect 200; Ergoline, GmbH, Germany)

**Fig. 3 Fig3:**
[figure not shown]
Screen shot of the display on the exercise ergometer at the end of a 40-minute exercise session. This shows power (W) and heart rate (beats.min-1) on the y-axis versus time (min) on the x-axis. The square wave pattern on the background is the preloaded exercise training programme. The sinusoidal pattern on the foreground is the variation in heart rate with the different training intensities recorded over time

### Outcome measurements

All patients undergo a series of outcome measure assessments throughout the period of the trial: baseline (pre-neoadjuvant CRT), mid-neoadjuvant CRT and at several time points following completion of the neoadjuvant CRT (weeks 0, 3, 6 and 9) prior to surgery (surgery generally takes place between weeks 6 and 9, depending on the hospital). In UHS only, based on the clinical pathway, some patients are treated with neoadjuvant chemotherapy (four cycles) followed by neoadjuvant CRT. In this instance, an additional research visit is scheduled halfway between the completion of chemotherapy and commencing CRT). The outcome measures used in the EMPOWER trial are summarised in Table 1.

**Table 1 Tab1:** Outcomes and assessment measures used in the EMPOWER trial

Outcomes	Assessment measure	Pre CRT	Mid chemo-CRT	Mid CRT	Week 0	Week 3	Week 6	Week 9	Day 3 post-surgery	Day 5 post-surgery	Day 8 post-surgery	Day 15 post-surgery	6 Weeks post-surgery
Primary endpoint													
Oxygen uptake at lactate threshold	CPET	X	UHS only		X	X	X	X					
Secondary endpoint													
Health-related quality of life	Questionnaires: EORTC QLQ-30, EQ-5D	X	UHS only	X	X	X	X	X					X
	Semi-structured interviews				X			X					
Physical activity	SenseWear accelerometer	X	UHS only	X	X	X	X	X					
Exploratory endpoint													
Post-operative morbidity	POMS								X	X	X	X	
Cancer staging	MR pelvis mrTRG	X						X					
								X					

*Abbreviations*: *CRT* chemoradiotherapy, *CPET* cardiopulmonary exercise test, *UHS* University Hospital Southampton, *POMS* Post- operative morbidity score, *mrTRG* magnetic resonance tumour regression grade, *MR* magnetic resonance

### Primary outcome

#### Physical fitness

CPET is used to assess physical fitness over a series of time points (which vary in each hospital depending on the cancer treatment and time interval between CRT and surgery): baseline (pre-neoadjuvant CRT); mid chemotherapy-CRT (in UHS only); and post-neoadjuvant CRT (week 0), week 3, week 6 and week 9. All CPETs are performed in the hospital by trained and experienced staff. Every effort is made to coordinate research visits with other clinical appointments. Each CPET is conducted at a similar time of day. Participants are asked to refrain from caffeine and strenuous exercise prior to the test. All CPETs are performed using an electromagnetically-braked cycle ergometer (Ergoline 2000), a 12-lead ECG, non-invasive blood pressure measurement and pulse oximetry, and a metabolic cart (Geratherm Respiratory GmbH, Love Medical Ltd). The incremental rise in work rate is pre-determined using the equation derived by Wasserman and colleagues [22] in which the same work-rate protocol is used for each CPET. This is done in an objective manner aiming for a test duration between 8 and 12 minutes. The ramp protocol equation is as follows:$$ \begin{array}{c}\hfill \overset{\cdotp }{\mathrm{V}}{\mathrm{o}}_2\kern0.24em \mathrm{unloaded}\kern0.24em \left(\mathrm{ml}.mi{n}^{-1}\right)=150+\left(6\times \mathrm{weight}\kern0.24em \left(\mathrm{kg}\right)\kern0.24em \right)\hfill \\ {}\hfill \overset{\cdotp }{\mathrm{V}}{\mathrm{o}}_2\kern0.24em \mathrm{at}\kern0.24em \mathrm{Peak}\kern0.24em \left(\mathrm{ml}.mi{n}^{-1}\right)\kern0.24em \mathrm{Men}=\left[\mathrm{height}\kern0.24em \left(\mathrm{cm}\right)-\mathrm{age}\left(\mathrm{y}\right)\right]\times 20\hfill \\ {}\hfill \overset{\cdotp }{\mathrm{V}}{\mathrm{o}}_2\; at\kern0.24em \mathrm{Peak}\left(\mathrm{ml}.mi{n}^{-1}\right)\kern0.24em \mathrm{Women}=\left[\mathrm{height}\kern0.24em \left(\mathrm{cm}\right)-\mathrm{age}\left(\mathrm{y}\right)\right]\times 14\hfill \\ {}\hfill \mathrm{Work}\kern0.24em \mathrm{Rate}\kern0.24em \mathrm{increment}\kern0.24em \left(\mathrm{W}.mi{n}^{-1}\right)=\mathrm{Peak}\kern0.24em \overset{\cdotp }{\mathrm{V}}{\mathrm{o}}_2-\left.\overset{\cdotp }{\mathrm{V}}{\mathrm{o}}_2\kern0.24em \mathrm{Unloaded}\right)/100\hfill \end{array} $$

Each participant receive instructions on how to rate the Borg Scale of perceived exertion (Scale 0 to 10), which is a subjective rating of breathlessness and for leg fatigue (assessed every 2 minutes during the test). Additionally, blood pressure is recorded every 2 minutes during the test. Saddle height is measured and recorded at the first CPET and remains constant for all other CPETs. Once the patient is comfortable on the bike, the mask is fitted. The patients are asked to perform an incremental ramp test to the limit of tolerance and to maintain a cycling cadence at 55–65 revolutions per minute (rpm) throughout the test. CPET allows for the derivation of lactate threshold using the modified V-Slope method [23, 24]. The modified V-Slope method identifies the lactate threshold as the tangential breakpoint in the rate of change of $$ {\overset{\cdotp }{V}}_{C{O}_2} $$ relative to $$ \overset{\cdotp }{\mathrm{V}}{\mathrm{o}}_2 $$ (oxygen uptake – carbon dioxide output) from the line of unity (‘line of one’) during the incremental stage of the exercise test. The V-slope methods depend solely on the physicochemical reaction of hydrogen ions with bicarbonate, and as such, the occurrence of the breakpoint is independent of the chemoreceptor sensitivity and the ventilatory response to exercise [23]. The inter-observer variability for experienced clinicians is very acceptable [25]. Two independent physiological data assessors are blind to group allocation and are independent to the intervention. The multi-disciplinary team caring for the patients are not provided with any information regarding outcome measures.

### Secondary outcome

#### Health-related quality of life (HRQoL)

HRQoL is assessed in two ways: 1) Semi-structured interviews are conducted at week 0 (following neoadjuvant CRT) and at weeks 6 to 9 (prior to surgery) to explore the patients’ perceptions of quality of life, which allows the patients to focus on personal accounts of their HRQoL within a specific context (for example, exercise participation and active cancer treatment). 2) HRQoL questionnaires are administered over several time points during the study: baseline (pre-neoadjuvant CRT), mid-chemotherapy CRT (in UHS only), mid-neoadjuvant CRT, post-neoadjuvant CRT (week 0), week 3, week 6, week 9 and 30 days post-surgery. The two questionnaires administered at these time points are the EORTC QLQ-30 and EQ-5D. EORTC QLQ-30 is specific to cancer patients and is validated to assess generic aspects of HRQoL. EQ-5D is a simple descriptive profile and a single index value for health status.

### Exploratory outcome measure

#### Physical activity

Daily physical activity is measured over three consecutive days and nights at a series of time points: baseline (pre-neoadjuvant CRT), mid-chemotherapy CRT (in UHS only), post-neoadjuvant CRT (week 0), week 3, week 6 and week 9. Physical activity is measured using a multi-sensory accelerometer ((SenseWear Pro® armband (Model MF-SW, display model DD100); BodyMedia, Inc., Pittsburgh, PA, USA)), which records daily movements, including total energy expenditure, physical activity duration, lying-down time, active energy expenditure, number of steps, sleep duration, total energy expenditure, degree of physical activity, average metabolic equivalent threshold (MET), duration of sensor on body, sleep efficiency, and physical activity level (PAL, which is the ratio of estimated daily energy expenditure to estimated basal metabolic rate).

#### Post-operative morbidity survey (POMS)

Post-operative outcomes will be objectively recorded using POMS on days 3, 5, 8 and 15. The POMS is a validated 18-item tool that addresses nine domains of morbidity relevant to the post-surgical patient: pulmonary, infection, renal, gastrointestinal, cardiovascular, neurological, wound complications, haematological and pain [26, 27]. For each domain, either the presence or absence of morbidity is recorded on the basis of precisely defined clinical criteria.

#### Cancer staging

Cancer down-staging will be assessed using the TNM classification. Rectal cancer staging will be assessed using an abdominal-pelvic CT scan and pelvic MRI scan pre-neoadjuvant CRT and at 9 weeks following completion of the neoadjuvant CRT. The TNM classification of malignant tumours is a cancer staging notation system that gives codes to describe the stage of a solid tumour [28].

### Safety

All adverse events are recorded in the relevant case report form. Adverse events during CPET are reported to the chief investigator, and adverse effects during exercise training (pain and muscle soreness) are recorded in the relevant case report form by the research physiologist/nurse. Fatal or life-threatening serious adverse events (SAEs) are reported within 24 hours of the local site becoming aware of the event. The SAE form documents the nature of the event, date of onset, severity, corrective therapies given, outcome and causality (that is, unrelated, unlikely, possibly, probably, or definitely). Questions concerning adverse event reporting are directed to the chief investigator in the first instance.

### Data analysis

#### Sample size calculation

A sample of 46 patients is required to detect a difference between groups of 2.0 mL.kg^-1.^min^−1^$$ \overset{\cdotp }{\mathrm{V}}{\mathrm{o}}_2 $$ at $$ {\widehat{\uptheta}}_{\mathrm{L}} $$ using a two-sample t-test at the 5 % significance level with 90 % power. This is based on a standard deviation of the change in $$ \overset{\cdotp }{\mathrm{V}}{\mathrm{o}}_2 $$ at $$ {\widehat{\uptheta}}_{\mathrm{L}} $$ values of 1.8 ml.kg^−1·^min^−1^ and is inflated to allow for 20 % patient drop-out [29]. This estimate was calculated using the sampsi function in Stata/IC 12.0.

#### Procedures for data checking and entering

Data will be double data entered, and data validation will take place according to the procedures set out in the data management plan and data validation plan. Prior to any statistical analysis, all variables will be checked for the number of missing values, impossible values and improbable values. Impossible and improbable values will be defined by clinical opinion. Improbable values will also include values that are outside three standard deviations of the mean value. Any questions regarding the data will go back to the data manager. Descriptive statistics will be calculated for all variables, and distributional assumptions will be checked.

#### Statistical analyses

Descriptive analyses will be carried out to summarise patient characteristics. Continuous variables will be reported as mean (range), mean (SD) or median and inter-quartile range (IQR), depending on distribution, and categorical variables as frequency (%). The effect of neoadjuvant CRT and the exercise intervention on physical fitness will be assessed using a two-sample t-test, and a 95 % confidence interval on the mean difference between the two groups will be presented. In order to assess the sensitivity of results to covariates, a further ‘adjusted’ effect will be calculated using linear regression where up to three candidate covariates will be identified [30]. Basic exploratory analysis of physical fitness at each time-point will be undertaken to investigate the longitudinal response of fitness. Linear mixed modelling will then be employed to compare more formally the fitness at each time-point. Confirmatory analysis using ordinal regression will be used to assess the suitability of the t-test for comparing the HRQoL between the groups. The effect of an in-hospital exercise training programme on physical activity will be analysed in the same way as physical fitness. The presence/absence of post-operative morbidity as defined by a POMS score > 0 will be compared between groups by calculating the relative risk with a 95 % confidence interval. Cancer staging will be reported as tumour, node metastasis version 5 (TNM) staging, Response Evaluation Criteria in Solid Tumours (RECIST) and MR tumour regression grading (mrTRG) criteria. Pathological outcomes will be graded according to the pathological tumour regression grading (TRG) and TNM. Univariate logistic regression analysis will be used to analyse the association between demographic variables (patient age and sex), MRI parameters and pathologic tumour response. This will enable the calculation of odds ratios (OR) for the probability of an unfavourable pathological outcome. Analyses of sensitivity, specificity, positive and negative likelihood ratios will be performed.

The Standard Protocol Items-Recommendations for Interventional Trials (SPIRIT) table provides an overview of the study conduct, review, reporting and interpretation and is presented in Table 2. The final report will follow the Consolidated Standards of Reporting Trials (CONSORT), as well as the Template for Intervention Description and Replication (TIDieR).

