### Secondary hypothesis

An in-hospital exercise training programme compared with a usual care control group (usual care; no formal exercise training) will result in an improvement in psychological health benefits as assessed using semi-structured interviews and questionnaires such as the EORTC QLQ-30 and EQ-5D following neoadjuvant CRT prior to cancer surgery.Neoadjuvant CRT will result in a reduction in $$ \overset{\cdotp }{\mathrm{V}}{\mathrm{o}}_2 $$ at $$ {\widehat{\uptheta}}_{\mathrm{L}} $$ as assessed using CPET.

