## Methods/Design

### Study design

The EMPOWER Trial is a parallel group randomised controlled trial in locally advanced rectal cancer patients undergoing both neoadjuvant CRT and elective surgery. The trial is funded by the National Institute for Health Research - Research for Patient Benefit Programme (PB-PG-0711-25093), approved by North West Centre for Research Ethics Committees (13/NW/0259) and registered with clinicaltrials.gov (NCT01914068).

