### Participants

Eligibility criteria for inclusion at cancer diagnosis include the following: age ≥ 18 years, with MR-defined, locally advanced (circumferential resection margin threatened), resectable rectal cancer (≥ T2N + M0), undergoing standardised neoadjuvant CRT; with no distant radiological defined metastasis. Exclusion criteria include the following: inability to give informed consent, non-resectable disease, distant metastasis, inability to perform CPET or bicycle exercise, and patients who declined surgery or neoadjuvant CRT or who received non-standard neoadjuvant CRT. Figure 1 provides an algorithm of the clinical pathway and the complete series of assessments for the duration of the trial.

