### Recruitment and randomisation

The EMPOWER trial is currently recruiting (start date is August 2013; end date is December 2015). All potentially eligible patients are being identified at multi-disciplinary meetings and approached with written information about the trial at the oncology/surgical outpatient appointment. Patients are contacted by telephone to provide additional information about the trial and to confirm their eligibility. If the patient chooses to participate in this trial, the first research visit is organised where written informed consent is obtained and all baseline measurements are undertaken. Following neoadjuvant CRT (week 0), patients are allocated to the in-hospital exercise training group or usual care control group. Patients are randomised (1:1) to either an in-hospital exercise training programme or usual care control group using the Trans European Network for patient randomisation in clinical trials system (TENAELA System).

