Background and rationale	The standard treatment pathway for locally advanced rectal cancer is neoadjuvant chemoradiotherapy (CRT) followed by surgery. Neoadjuvant CRT has been shown to decrease physical fitness, and this decrease is associated with increased post-operative morbidity. Exercise training can stimulate skeletal muscle adaptations such as increased mitochondrial content and improved oxygen uptake capacity, both of which contribute to physical fitness. The aims of the EMPOWER trial are to assess the effects of neoadjuvant CRT and an in-hospital exercise training programme on physical fitness, health-related quality of life (HRQoL), and activity levels, as well as post-operative morbidity and cancer staging.
Comparators	The usual care control group (usual care – no formal exercise training) receive routine care throughout their cancer pathway from diagnosis to surgical resection. No specific advice about exercise training is offered.
Objectives	The aims of this study were to evaluate the following hypotheses:
	Primary hypothesis: A 9-week in-hospital exercise training programme compared with a usual care control group (usual care - no formal exercise training) will result in a clinically significant difference in oxygen uptake at lactate threshold ($$ \overset{\cdotp }{\mathrm{V}}{\mathrm{o}}_2 $$ at $$ {\widehat{\uptheta}}_{\mathrm{L}} $$ ; 2.0 mL.kg^-1.^min^−1^) assessed using CPET, following neoadjuvant CRT prior to elective cancer surgery.
	Secondary hypothesis: a) An in-hospital exercise training programme compared with a usual care control group (usual care - no formal exercise training) will result in an improvement in psychological health benefits assessed using semi-structured interviews and questionnaires such as EORTC QLQ-30 and EQ-5D, following neoadjuvant CRT prior to cancer surgery. b) Neoadjuvant cancer treatment will result in a reduction in $$ \overset{\cdotp }{\mathrm{V}}{\mathrm{o}}_2 $$ at $$ {\widehat{\uptheta}}_{\mathrm{L}} $$ assessed using CPET.

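### The two-sample t-test between the arms is named for the effect of neoadjuvant CRT, but every patient has CRT before randomisation, so it cannot test the secondary hypothesis on CRT

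*Protocol article*

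**What the plan says.** The protocol article, Statistical analyses, gives one method for two effects: "The effect of neoadjuvant CRT and the exercise intervention on physical fitness will be assessed using a two-sample t-test", and adds that "a 95 % confidence interval on the mean difference between the two groups will be presented". The Statistical methods row of Table 2 (SPIRIT) carries the same sentence. The only groups that the article defines are the exercise arm and the usual care arm.

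The effect of CRT is a stated hypothesis. The Secondary hypothesis section says "Neoadjuvant CRT will result in a reduction in" oxygen uptake at lactate threshold. The Objectives row of Table 2, where it is labelled (b), words the cause differently: "Neoadjuvant cancer treatment will result in a reduction in" the same measure.

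On exposure and timing:

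- Study design describes the population as "locally advanced rectal cancer patients undergoing both neoadjuvant CRT and elective surgery".
- The exclusions under Participants include "patients who declined surgery or neoadjuvant CRT or who received non-standard neoadjuvant CRT".
- Recruitment and randomisation says "Following neoadjuvant CRT (week 0), patients are allocated to the in-hospital exercise training group or usual care control group".
- Table 1 schedules cardiopulmonary exercise testing (CPET) pre-CRT, at week 0 and at weeks 3, 6 and 9.
- At University Hospital Southampton (UHS), "some patients are treated with neoadjuvant chemotherapy (four cycles) followed by neoadjuvant CRT". These patients have an extra visit between the two treatments, and Table 1 includes CPET at it.

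After the t-test, Statistical analyses also plans a linear mixed model comparing fitness across the time points. It does not say which hypothesis that model serves.

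**The concern.** Hypothesis (b) concerns a change within patients from before CRT to after it. The named test compares two arms formed once CRT is over. Nobody in the trial goes without CRT, so no between-group contrast carries information about its effect.

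An analyst who follows the text literally would report the difference between exercise and usual care as bearing on the CRT effect. A null result could then be read as evidence that CRT does not reduce fitness, when the test could not have shown it. An analyst who sees the problem would have to choose another method, possibly after seeing the data. The effect of CRT on fitness is among the aims in the Abstract and returns in the Discussion, so the wording matters even though the hypothesis is secondary.

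**Working it through.** **1. The plan's own figure.** Inputs from Sample size calculation: difference 2.0 mL/kg/min, SD of change 1.8, 5 % significance level (taken as two-sided, since sidedness is not stated), 90 % power, 20 % drop-out.

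- n per arm = 2 × [1.8 × (1.960 + 1.282) / 2.0]² = 17.02, rounded up to 18.
- Allowing for drop-out: 18 / 0.8 = 22.5, rounded up to 23 per arm, or 46 in total.
- Exact t-test power at 18 per arm is 0.899.

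The stated 46 reproduces. It is built on the difference between arms, that is, on the exercise comparison.

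**2. What the between-arm test estimates.** Let δ be the mean change caused by CRT, and let e and c be the mean changes after week 0 under exercise and usual care.

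- Change from pre-CRT to week 0: expectation δ in each arm, so the difference is δ − δ = 0.
- Change from pre-CRT to a later week: (δ + e) − (δ + c) = e − c, which is the exercise effect only.

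The first line needs no assumed SD or correlation. It holds even if CRT affects patients differently, because randomisation at week 0 balances that variation in expectation. It does require that the week-0 CPET precedes training, which fits the article's use of that test to set training intensity.

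**3. Simulation check.** 20,000 trials, 23 patients per arm, the same CRT effect in both arms. The SD of the CRT-period change was assumed to be 1.8. That value is borrowed from the sample size section, as the article gives none for this period.

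| Common CRT effect (mL/kg/min) | Mean between-arm difference | Between-arm test rejects | Paired test, all 46, rejects |
|---|---|---|---|
| 0 | -0.005 | 5.0 % | 5.1 % |
| -1 | -0.006 | 5.1 % | 96.0 % |
| -2 | 0.000 | 5.0 % | 100 % |
| -4 | -0.002 | 5.0 % | 100 % |

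The between-arm test stays at its error rate however large the CRT effect is.

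**4. What a within-patient contrast offers on the same data.** With the same assumed SD, SE = 1.8/√46 = 0.265 with 46 patients and 1.8/√36 = 0.300 with 36, the total before the drop-out allowance. Exact power of the paired t-test:

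| Fall (mL/kg/min, illustrative) | 36 patients | 46 patients |
|---|---|---|
| 0.5 | 0.37 | 0.45 |
| 1.0 | 0.90 | 0.96 |
| 1.5 | >0.99 | >0.99 |
| 2.0 | >0.99 | >0.99 |

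The article states no expected CRT effect, so these figures show only that the trial could address (b) with a suitable analysis.

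**5. The two wordings of the hypothesis.** If (b) concerns CRT alone, the reference for UHS patients given chemotherapy first is the CPET between chemotherapy and CRT. If it concerns all neoadjuvant treatment, the reference is the first baseline. The wording in the Secondary hypothesis section points to the former and that in Table 2 to the latter.

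**The case against.** The best reply is that a usable analysis is already planned. The mixed model compares fitness across time points that include pre-CRT and week 0, so it can supply the within-patient contrast. This stands, and it limits the point. A reader might infer that hypothesis (b) is left with no valid analysis. The article does not support that: the fault lies in the method named for the CRT effect and in the missing link between the mixed model and the hypothesis.

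Three other inferences are tempting and also go too far.

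- **That pre- and post-CRT values would be treated as independent samples, losing precision.** The interval is placed on the difference between the two groups, and the only groups are the arms. Nothing proposes that analysis, and costing it would need a pre-post correlation that the article does not give.
- **That loss of fitness from chemotherapy at UHS would be credited to CRT.** This assumes that the first baseline serves as the CRT reference for those patients. No section fixes the reference visit, and the extra CPET provides a suitable one. The number affected is not given. What remains is the mismatch in wording.
- **That the main result is compromised.** The primary hypothesis is the exercise comparison, for which a two-sample t-test is suitable.

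Nor can the point be left to a separate analysis plan as omitted detail, because the article does choose a test for the CRT effect, in two places, and the choice is wrong.

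**Conclusion.** The point holds for the analysis named for hypothesis (b). The between-arm t-test has expectation zero for any CRT effect, and its power equals the 5 % error rate. This rests only on the design: CRT for everyone, and allocation afterwards. The paired power figures are illustrative, since they rest on an assumed SD of 1.8 for the CRT period and on assumed falls.

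One secondary hypothesis is affected. The primary comparison and the sample size of 46 are not. No data are lost, and a suitable model is already in the plan. It should be fixed, but it does not threaten the trial's main conclusion.

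Even when analysed correctly, (b) remains an uncontrolled before-after comparison, so a fall cannot be attributed to CRT alone.

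**What to change.** 1. In Statistical analyses and in the Statistical methods row of Table 2, restrict the two-sample t-test to the effect of the exercise intervention.
2. For hypothesis (b), name the mean within-patient change in oxygen uptake at lactate threshold from pre-CRT to week 0, all patients pooled over arms, with a 95 % confidence interval. Use either a paired t-test or the week-0 minus pre-CRT contrast of the planned mixed model, and say which before the data are analysed.
3. Describe this as an uncontrolled before-after comparison.
4. Make the Secondary hypothesis section and the Objectives row of Table 2 agree on whether CRT alone or all neoadjuvant treatment is meant. If CRT alone, use the existing CPET between chemotherapy and CRT as the reference for UHS patients who had chemotherapy first.

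The cost is a few sentences. The CPETs are already scheduled, and no change to recruitment or sample size is needed.

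### The main comparison of VO2 at lactate threshold is an unadjusted t-test that does not say change or final value; adjusting for the week-0 value already collected would be modestly more precise

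*Protocol article*

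**What the plan says.** Under Statistical analyses, and again in the statistical methods row of Table 2, the effect on physical fitness is assessed by a two-sample t-test with a 95 % confidence interval for the mean difference between groups. Neither place says whether the variable tested is a change or a final value.

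Adjustment is a secondary step, there to show how sensitive the result is to covariates: a further adjusted "effect will be calculated using linear regression where up to three candidate covariates will be identified". The week-0 value is not named in any model. A linear mixed model follows, for comparing fitness at each time point, but it is not presented as the main comparison.

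The sample size section is more specific about the scale: "This is based on a standard deviation of the change in" VO2 at lactate threshold, with the value 1.8 mL/kg/min. It states "A sample of 46 patients is required to detect a difference between groups of 2.0" mL/kg/min, "using a two-sample t-test at the 5 % significance level with 90 % power", "and is inflated to allow for 20 % patient drop-out".

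Recruitment and randomisation places allocation after chemoradiotherapy, at week 0. Outcome measurements and Table 1 schedule the cardiopulmonary exercise test at week 0 for all patients.

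**The concern.** The week-0 value is the primary endpoint measured just before the intervention starts, so it is the natural covariate for the exercise effect. The plan collects it for everyone and then leaves it out of the main model as written.

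Two things follow. First, precision is given up: with about 18 completers per arm, a t-test on change corrects fully for the week-0 value (slope fixed at 1), whereas ANCOVA uses the slope that minimises residual variance. Second, the article leaves two readings of its main test open. They agree at a correlation of 0.5 and diverge quickly above it, and only the change reading matches the standard deviation used for the sample size.

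**Working it through.** **Inputs.** From Sample size calculation: difference 2.0, SD of change 1.8, 5 % level, 90 % power, 20 % drop-out. From Recruitment and randomisation: 1:1 allocation. Assumed: a two-sided test (sidedness is not stated), equal variances at week 0 and at the end, and a correlation ρ between the two values, which the document does not give; the range used is 0.5 to 0.9.

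**1. Reproduce the 46.** Normal approximation, per arm: n = 2 × [1.8 × (1.960 + 1.282) / 2.0]² = 17.02, rounded up to 18. With drop-out: 18 / 0.8 = 22.5, rounded up to 23 per arm, so 46 in total. The stated figure holds. A one-sided test would need 14 per arm, which does not fit.

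**2. t-test on change, 18 completers per arm.** Standard error = 1.8 × √(2/18) = 0.60; noncentrality = 2.0 / 0.60 = 3.33; 34 degrees of freedom. Noncentral-t power is 89.9 %.

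**3. What an SD of change of 1.8 implies.**
- SD of a single value: s = 1.8 / √(2(1 − ρ)).
- ANCOVA residual SD: s × √(1 − ρ²).
- ANCOVA variance over change-score variance: (1 + ρ)/2.
- ANCOVA variance over final-value variance: 1 − ρ².

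**4. Charge ANCOVA for the covariate.** One degree of freedom is lost (33 remain), and the expected variance is multiplied by 1 + 1/(2n − 4) = 1 + 1/32 = 1.031.

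| ρ (assumed) | SD of final value | ANCOVA residual SD | Power, t-test on change | Power, ANCOVA on week 0 | Power, t-test on final values | Net variance, ANCOVA / change |
|---|---|---|---|---|---|---|
| 0.5 | 1.80 | 1.56 | 89.9 % | 95.7 % | 89.9 % | 0.77 |
| 0.6 | 2.01 | 1.61 | 89.9 % | 94.5 % | 82.5 % | 0.83 |
| 0.7 | 2.32 | 1.66 | 89.9 % | 93.3 % | 70.8 % | 0.88 |
| 0.8 | 2.85 | 1.71 | 89.9 % | 91.9 % | 53.5 % | 0.93 |
| 0.9 | 4.02 | 1.75 | 89.9 % | 90.5 % | 30.5 % | 0.98 |

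**5. Where the gain ends.** Setting (1 + ρ)/2 × 1.03125 = 1 gives ρ = 2/1.03125 − 1 = 0.94.

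**6. Adding hospital.** Table 2 lists five hospitals, so separate terms cost four more degrees of freedom. With five covariates in all, the variance factor is 1 + 5/28 = 1.179 with 29 degrees of freedom. If hospital explains nothing, power at ρ = 0.7 is 89.6 %, slightly below the change-score t-test. One pooled hospital term (factor 1 + 2/31 = 1.065) gives 92.5 %.

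**The case against.** The strongest reply is that the plan is coherent as it stands. The sample size section powers a two-sample t-test on an SD of change and the analysis section names the same test, so the natural reading is a t-test on change. That test already uses each patient's earlier value and is valid under randomisation, and it matches its own sample size. The plan also contains a mixed model over repeated measurements. All of this stands, and it limits the point to efficiency and clarity.

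Stronger readings are tempting, but the documents do not support them:

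- **That the trial really has 54 to 83 % power.** Those figures need unadjusted final values and ρ of 0.6 to 0.8. The article never says final values are tested, and the SD of change makes that the less natural reading.
- **That the unnamed covariates leave room to choose the result.** They belong to a sensitivity analysis, are capped at three, and may be named in an analysis plan not shown. Nothing says they are chosen after seeing results, and the Discussion says the statisticians stay blind to allocation until the analysis is complete.
- **That the exercise effect is measured from the wrong baseline.** The article uses the word baseline for the pre-chemoradiotherapy visit, but nowhere says the exercise effect is calculated from it.
- **That hospital must be in the model because programme length is "dependent on the time interval between neoadjuvant CRT and surgery at each hospital".** Step 6 shows that separate terms for five hospitals could cancel the gain.
- **That the planned ordinal regression for quality of life adds weight.** It concerns a secondary endpoint and has no bearing on this comparison.

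**Conclusion.** The point holds as one of efficiency and wording. The t-test is not invalid and the sample size is not wrong. Against a t-test on change, week-0 adjustment raises power at 18 per arm from 89.9 % to between 91.9 and 95.7 % for ρ of 0.8 to 0.5. After the covariate is paid for, the standard error falls by about 4 to 12 % (1 − √0.93 to 1 − √0.77). At ρ = 0.9 the gain is about 1 %, and it disappears only near 0.94. Adjustment also matters as protection: it makes the choice between change and final values irrelevant to the primary result, and that choice is costly if ρ is well above 0.5. The size rests on the assumed ρ, equal variances at the two times, a two-sided test and 36 completers.

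**What to change.** In Statistical analyses and in Table 2, make the primary analysis an ANCOVA of pre-surgery VO2 at lactate threshold on arm and week-0 VO2 at lactate threshold, or the equivalent mixed-model contrast, with a 95 % confidence interval for the arm difference. Keep the two-sample t-test as a sensitivity analysis and state that it is on change from week 0. Do not require separate hospital terms.

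This changes wording only: no new data, visits or patients, and the 46 can stand. The statistical price is one degree of freedom, about 3 % in variance.
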